**Methods:**

Patients with OI type I (the mildest form of OI; n=12, aged 12-16 years) from a pediatric orthopedic tertiary hospital will be randomized to receive a 12-week remote exercise intervention in either (1) a supervised group (n=6), monitored every session, or (2) a follow-up group (n=6), receiving monthly progress update appointments. Participants will undergo the following pre- and postintervention evaluations: sit-to-stand test, push-up test, sit-up test, single-legged balance test, and a heel-rise test. Both groups will be given the same 12-week exercise regimen, which includes cardiovascular, resistance, and flexibility training. For each exercise training session involving the supervised group, a kinesiologist will provide instructions to participants through live video sessions using a teleconferencing application. On the other hand, the follow-up group will discuss their progress with the kinesiologist every 4 weeks over a teleconferencing video call. Feasibility will be assessed by recruitment, adherence, and completion rates. A cost-effectiveness analysis of both approaches will be computed. Changes in muscle function and cardiopulmonary fitness will be examined between the 2 groups, pre- and postintervention.

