#### Cost-Effectiveness

To compare the cost-effectiveness of the 2 telemedicine approaches, a bottom-up approach will be used, a method for the assessment of each resource required to provide health care and assigning the related costs accordingly [21,22]. For both the supervised and follow-up groups, the mean performance outcome for each of the 5 preintervention evaluation tests will be computed. These means are then compared within their group (supervised or follow-up) to a mean for the same 5 postintervention evaluations, determining the mean outcome (increase or decrease) for each of the 5 tests. These mean outcomes will then be compared to the total cost of each telemedicine approach to determine the cost (on a per-unit basis) of the health outcome. Doing so allows for the assessment of not only which telemedicine approach has a higher cost overall, but most importantly, the per-unit cost of the health outcome for the supervised and follow-up groups. This provides a more accurate comparison, with respect to financial costs, of the 2 methods.

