### Statistical Analysis

As this is a feasibility study, the testing procedure will be assessed rather than only focusing on the potential outcomes of the intervention. To determine the optimal clinical practice of telemedicine for an exercise intervention, recruitment, adherence, and completion rates of 2 randomized groups (supervised and follow-up approaches) will be investigated. Descriptive statistics will be presented as means and SDs. Based on previous research on home-based exercise interventions [23], the adherence rate will be assessed with a set threshold of 80%. A Wilcoxon rank sum test will be used to evaluate the adherence rate and compare both telemedicine approaches. Whereas both recruitment and completion rates will be compared using descriptive statistics and assessed with a set threshold of 50%. To measure the change in outcome parameters of participants’ muscle strength and cardiopulmonary fitness, pre- and postintervention evaluation results will be assessed with a Friedman ANOVA. A Kruskal-Wallis test will be used to determine the differences in outcome parameter changes between the 2 groups (supervised and follow-up groups).

To assess the cost-effectiveness of the 2 telemedicine approaches, a cost-effectiveness plane and an incremental cost-effectiveness ratio will be computed. The incremental cost and incremental effect will be plotted on a cost-effectiveness plane, where the horizontal axis will represent the incremental cost and the vertical axis will represent the incremental effect [24,25]. The costs and clinical outcomes for both telemedicine groups will be plotted on the plane, which will visually demonstrate the additional cost per unit of health gain for each telemedicine approach. To calculate the incremental cost-effectiveness ratio, the difference in costs will be divided by the difference in mean performance outcomes between the supervised and follow-up groups.

Finally, as OI is classified as a rare disorder [1], analyses will be carried out with a significance level (α) of 0.10 [26]. Statistical analyses will be conducted using the statistical analysis software SPSS, version 25 (SPSS Inc).

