**Microsoft Teams**			
	Per group	74 (55)	74 (55)
	Per participant	12 (9)	12 (9)
Total group cost estimation		4420 (3284)	3340 (2482)
Total per participant cost estimation		736 (547)	556 (414)

Estimated cost comparison breakdown per telemedicine approach.

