## Discussion

### Overview

The aim of this study is to evaluate the feasibility of 2 telemedicine approaches for the delivery of a home-based exercise program and determine the most cost-effective approach. The secondary aim of the study is to investigate the effect of a home-based exercise program on muscle function and cardiopulmonary fitness in youth with OI type I. Given the aims of the study, it is hypothesized that the supervised group will have higher adherence and completion rates compared to the follow-up group, and therefore, the physiological benefits will be greater in the supervised group than the follow-up group due to additional benefits from constant supervision. However, the follow-up group will receive individual attention in contrast to the supervised group, in which the specialist will work with groups of 3 patients. Direct comparison of patient performance in the supervised and follow-up groups will allow us to identify which telemedicine approach is more cost-effective and efficient for the delivery of an exercise program to OI pediatric patients.

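### The incremental cost-effectiveness ratio is a point ratio from 6 versus 6 participants, with no uncertainty and no value per unit, so it cannot support the promise to name the more cost-effective approach

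*Protocol article*

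**What the plan says.** Cost-effectiveness of the two approaches is part of the first main objective (Abstract, Objective). The design compares "a supervised group (n=6), monitored every session, or (2) a follow-up group (n=6), receiving monthly progress update appointments".

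Under Statistical Analysis, "a cost-effectiveness plane and an incremental cost-effectiveness ratio will be computed", and for the ratio "the difference in costs will be divided by the difference in mean performance outcomes between the supervised and follow-up groups". That section sets thresholds for adherence, recruitment and completion, names tests for adherence and function, and fixes the significance level at 0.10. For the ratio it gives no interval, no resampling and no value per unit gained.

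The Cost-Effectiveness section adds a second quantity, "the per-unit cost of the health outcome for the supervised and follow-up groups". It is obtained after "determining the mean outcome (increase or decrease) for each of the 5 tests".

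In Table 2, the row "Total per participant cost estimation" shows CAD 736 for supervised and CAD 556 for follow-up. These are estimates; the Cost section says that the kinesiologist's hours will be recorded.

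The Discussion (Overview) then says that directly comparing performance in the two groups "will allow us to identify which telemedicine approach is more cost-effective and efficient for the delivery of an exercise program".

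**The concern.** The two parts of the ratio behave very differently. The numerator is largely set by the delivery schedule: 76 planned intervention hours for supervised against 36 for follow-up. The denominator is a difference between two means of six and may well lie near zero, where a quotient is unstable and can change sign.

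If supervision costs more, an estimated effect below zero makes follow-up cheaper and better. An estimated effect above zero gives a price per repetition or per second, and the article offers nothing to compare that price with. A reader of the results would be unable to tell a real cost-effectiveness difference from noise on a main objective, while the Discussion has already promised an answer.

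**Working it through.** **1. Reproduce the cost figures (cost breakdown and Table 2).**
- Kinesiologist, supervised: (24 + 76) h × CAD 27 = 2,700. Follow-up: (24 + 36) h × CAD 27 = 1,620.
- Equipment per group: 274.28 × 6 = 1,645.68. Microsoft Teams per group: 18.40 × 4 = 73.60.
- Totals: 4,419.28 and 3,339.28, which match the printed 4,420 and 3,340 apart from rounding.
- Difference: 1,080 per group, and 1,080 / 6 = CAD 180 per participant, the same as 736 − 556.

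**2. Assumptions for the effect.** The article gives no SD or effect size. Let d be the true supervised advantage on one test, in SDs of the change score. Assume normal changes, equal SDs and six analysed per arm. The standard error of the difference is sqrt(2/6) = 0.577 SD.

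**3. Chance that the effect difference is negative**, Φ(−d / 0.577):

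| d | 6 per arm | 60 per arm |
|---|---|---|
| 0 | 50% | 50% |
| 0.2 | 37% | 14% |
| 0.5 | 19% | 0.3% |
| 0.8 | 8% | <0.1% |
| 1.0 | 4% | <0.1% |

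The first row does not depend on sample size. The rows with d > 0 are wrong-sign results, and these do come from the small sample.

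**4. Precision of the effect.** The 90% half-width is 1.812 × 0.577 = 1.05 SD (t with 10 df). I use 90% to match the significance level of 0.10, read as two-sided.

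**5. Does the ratio have a usable interval?** With the cost difference taken as fixed, a Fieller interval is bounded only if the 90% interval for the effect excludes zero. From the noncentral t (10 df, noncentrality d / 0.577), this happens in 10% of trials at d = 0, 21% at 0.5, 36% at 0.8 and 49% at 1.0.

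**6. Spread of the point ratio.** At d = 0.5 the true ratio is 180 / 0.5 = CAD 360 per SD. In simulation the estimated ratio has a 5th percentile of −1,542, a median of 227 and a 95th percentile of 1,809.

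**7. The per-unit cost comparison.** Supervised is cheaper per unit when its gain exceeds 736 / 556 = 1.32 times the follow-up gain (both gains positive). If the true gains are equal, at 0.5 to 1.5 SD, follow-up is truly cheaper per unit; the point estimates still name supervised in 40% to 24% of trials. With a supervised advantage of 0.5 SD on the same follow-up gains, they name supervised in 69% to 51%.

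**8. Dependence on a value per unit.** Incremental net benefit is λ × (effect difference) − 180. At d = 0.5 it is truly zero at λ = 360 per SD. Over an assumed range of λ from 180 to 1,800 per SD, the point estimate favours supervised in 19% to 76% of trials. The answer turns on a value that the article does not state.

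**The case against.** **The plan can only ever favour follow-up.** A reader might infer this from the sign argument, but the documents do not support it. The article states no rule for turning the ratio into a choice; dominance is only the usual reading of the plane. The per-unit cost comparison can name supervised. That supervision costs more is also an estimate until the hours are recorded, though a likely one.

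**With equal effects the result is a coin-flip.** This is true of the sign for one test, but at any sample size. It also names no wrong approach: if effects are equal and supervision costs more, follow-up is the more cost-effective choice. With five tests and equal effects, the signs are mixed in 51% to 94% of trials (assumed correlation 0.7 to 0), so one sign does not decide the study.

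**Intervals and value thresholds may stand in a fuller plan.** They may, and their absence from an article would be a weak point alone. What remains is printed text: a formula for a bare ratio, and an unqualified promise of what the comparison will show.

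**This is a pilot, and its limits are admitted.** The Limitations section says that 12 participants may not support strong conclusions, but it says so about the data on muscle function and cardiopulmonary fitness. It does not mention cost-effectiveness, and the Discussion claim is left unqualified.

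**Conclusion.** The concern holds in limited form. A point ratio of mean differences from 6 versus 6, with no uncertainty and no value per unit, cannot support the statement that the study will show which approach is more cost-effective. On Table 2 costs, the ratio alone settles the matter only when follow-up dominates. For one test at an assumed true benefit of 0.5 SD, the sign is wrong in about 19% of trials, a bounded 90% interval for the ratio exists in about 21%, and the effect is known only to within about ±1.05 SD. The per-unit cost comparison does not rescue the conclusion, because it carries the same noise and also has no interval.

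These sizes rest on assumed effects in SD units, normal changes, complete data on 12 participants and a cost gap near the estimate. The finding does not show bias towards follow-up. It bears on one main objective and leaves the feasibility outcomes untouched.

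**What to change.** In Statistical Analysis:
- For each of the five tests, report incremental cost and incremental effect separately, with a 90% interval for the effect (t-based, or by resampling participants within arm).
- Show the joint uncertainty on the cost-effectiveness plane.
- Present incremental net benefit over a stated range of values per unit gained, in place of reliance on the single ratio.

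In the Discussion (Overview), replace the promise to determine the more cost-effective approach with an aim to estimate, with its uncertainty, the incremental cost and effect of the two approaches.

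This changes analysis and wording only and needs no new data. The small downside is that the result will probably be reported as inconclusive. The range of values per unit must be chosen by the investigators, since the article offers none.

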## Results

As the costs associated with both telemedicine approaches can be estimated, the anticipated cost comparison and breakdown of each approach are summarized below (Table 2 and Textbox 1).

**Table 2 table2:** Estimated cost comparison per telemedicine approach.

Cost estimations		Supervised group, CAD $ (US $)	Follow-up group, CAD $ (US $)
**Kinesiologist**			
	Per group	2700 (2006)	1620 (1204)
	Per participant	450 (334)	270 (201)
**Equipment**			
	Per group	1646 (1223)	1646 (1223)
	Per participant	274 (204)	274 (204)
**Microsoft Teams**			
	Per group	74 (55)	74 (55)
	Per participant	12 (9)	12 (9)
Total group cost estimation		4420 (3284)	3340 (2482)
Total per participant cost estimation		736 (547)	556 (414)

Estimated cost comparison breakdown per telemedicine approach.
**Kinesiologist**
Evaluations2 hours (preintervention evaluation)+2 hours (postintervention evaluation)×6 participants=24 hoursInterventionEstimated time required for the supervised approach
(8 hours [month 1]+12 hours [month 2]+18 hours [month 3])×2 (number of groups)=76 hours
24 hours (evaluations)+76 hours (intervention)=100 hours
Total: 100 hours (total hours)×CAD $27 (US $20) (hourly rate)=CAD $2700 (US $2006)
Estimated time required for the follow-up approach
(2 hours [month 1]+2 hours [month 2]+2 hours [month 3])×6 (number of participants)=36 hours
24 hours (evaluations)+36 hours (intervention)=60 hours
Total: 60 hours (total hours)×CAD $27 (US $20) (hourly rate)=CAD $1620 (US $1204)

**Equipment**
Per participant: CAD $8.30 (US $6.17) (resistance band)+CAD $258.75 (US $192.26) (polar watch)+CAD $7.23 (US $5.37) (weighted ball)=CAD $274.28 (US $203.80)Per approach: CAD $274.28 (US $203.80) ×6 (number of participants)=CAD $1646 (US $1223)
**Microsoft Teams**
Per approach: CAD $18.40 (US $13.67) (monthly subscription fee)×4 (number of months)=CAD $74 (US $55)

## Discussion

### Overview

The aim of this study is to evaluate the feasibility of 2 telemedicine approaches for the delivery of a home-based exercise program and determine the most cost-effective approach. The secondary aim of the study is to investigate the effect of a home-based exercise program on muscle function and cardiopulmonary fitness in youth with OI type I. Given the aims of the study, it is hypothesized that the supervised group will have higher adherence and completion rates compared to the follow-up group, and therefore, the physiological benefits will be greater in the supervised group than the follow-up group due to additional benefits from constant supervision. However, the follow-up group will receive individual attention in contrast to the supervised group, in which the specialist will work with groups of 3 patients. Direct comparison of patient performance in the supervised and follow-up groups will allow us to identify which telemedicine approach is more cost-effective and efficient for the delivery of an exercise program to OI pediatric patients.

Greater adherence rates can be associated with benefits such as increased positive reinforcement, improved exercise techniques, and higher self-efficacy [12]. Furthermore, direct supervision is associated with a greater overall volume of exercise achieved and potentially more efficient training, as with this approach, clinicians have the ability to adjust exercises in real time to prevent injury or pain [12]. However, in the follow-up approach, there is schedule flexibility, as participants can perform the intervention sessions when it’s most convenient to them. As well, participants may develop autonomy by completing these sessions independently, which in the long term may lead to long-lasting physical activity as individuals feel more confident in their abilities to exercise on their own. Whereas participants in the supervised group rely on study personnel for instruction and motivation and may not develop the same level of autonomy as individuals in the follow-up group. Although there are several health benefits associated with direct supervision, these advantages may not outweigh the increased cost associated with this approach. Thus, the insight gained from this study into the level of participant supervision necessary for a telemedicine approach to be effective will satisfy the current gap in literature. The results pertaining to the feasibility and cost-effectiveness of both the supervised and follow-up telemedicine approaches will provide clinicians with fundamental knowledge regarding which approach is most feasible for the remote delivery of care to a pediatric and youth population.

To date, little is known about the potential effectiveness of exercise for children and adolescents with OI. Previous research has shown that children and adolescents with OI type I experience muscle weakness in addition to bone fragility [4]. Consequently, this muscle weakness may contribute to bone fragility elicited by the genetic mutation in the *COL1A1* or *COL1A2* genes [5]. Given the severe bone fragility in patients with OI and the strong positive relationship between muscle force and bone strength, therapies aiming to improve muscle force may lead to an increase in bone strength [5]. The results of this study will shed light on the physiological response to exercise in children and adolescents with OI. Takken et al [27] evaluated cardiopulmonary fitness and muscle strength in children and adolescents with OI type I and determined that cardiopulmonary exercise tolerance and muscle strength were significantly reduced in patients with OI. To the best of our knowledge, Van Brussel et al [8] is the only published study which demonstrated significant improvements in both aerobic capacity and muscle force and reduced fatigue levels in children and adolescents with OI type I and type IV following a 12-week supervised exercise program. On the contrary, from 2 different OI mice models, results from Tauer et al [28] and Gremminger et al [29] showed very mild improvements in muscle force and tolerance to fatigue following long-term (multiple weeks) exercise training, suggesting that in OI, there may be a decreased physiological response to exercise. Results from the proposed study will further build upon Van Brussel et al [8], providing insight into the frequency and intensity of the stimulus required to trigger physiological improvements following a 12-week exercise program for youth with OI type I.

### Limitations

The limitations of this study are the technical difficulties associated with telemedicine that may arise for both study personnel and participants, such as a poor internet connection, which may lead to low-quality, incomplete, or missed training sessions for those in the supervised group. For the follow-up group, a limitation to consider is the potential that participants will not wear the heart rate monitor during the sessions, as there will not be any direct supervision to provide reminders. This would lead to missed training data, limiting the quantity of data available for comparison between the 2 groups. Although this study was designed primarily to assess the feasibility of delivering a home-based exercise intervention through telemedicine, the data collected regarding the potential change in muscle function and cardiopulmonary fitness and the small sample size of only 12 participants may limit the ability to draw any strong conclusions. As well, given the narrow age range, the results of this study are not a predictor of younger or older patient populations; therefore, a larger-scale study would be beneficial. However, given the paucity of data regarding the physiological response to exercise in youth with OI, preliminary data will provide the basis for a larger intervention study. Additionally, as OI is primarily characterized by bone fragility, given this study’s remote delivery methods, it is not possible to assess the skeletal response to the 12-week exercise program. Thus, to build upon this study and given the skeletal deficits associated with OI, future research should investigate the impact of an exercise program on bone mineral content in individuals with OI. Recent research from Sinkam et al [30] demonstrated reduced mechanical tendon properties in a dominant severe OI mouse model. Given these results and the fact that tendons are typically rich in collagen type I, in addition to investigating skeletal parameters, researchers should evaluate the physiological response of tendons in OI from an exercise intervention.

The completion of a 12-week exercise program may present a challenge for some participants, especially during the final 4 weeks of the exercise intervention when the number of sessions increases to 3 times per week. To mitigate this potential concern, study participants in the supervised group will have the flexibility of completing missed training sessions on their own schedule and therefore have access to the exercise plan with detailed instructions, images, and videos of each exercise. Whereas participants in the follow-up group are given the flexibility of completing the training sessions when convenient to the individual rather than a rigid weekly schedule.

### Conclusion

Telemedicine provides health care professionals with the opportunity to deliver consistent care to individuals with rare disorders, such as OI, who may have previously been unable to obtain access to such treatments. Given that the COVID-19 pandemic has imposed great challenges in the delivery of health care, this study will provide beneficial insight into the feasibility and cost-effectiveness of remote health care delivery methods. If this study is successful, guidelines and recommendations may emerge, providing individuals with OI with a higher level of targeted care geared toward increasing their quality of life. Finally, the results of this study may be advantageous for the treatment of other rare disorders, furthering the possibility to provide access to care to a far greater patient population.

